10.1.6.2 Sleep/wake information

Sleep-wake rhythm information will be investigated using the following actigraph during the prior and switchover periods.

Equipment used: MicroTag activity meter MTN-221 manufactured by Accors Inc.

The subject wears the ACTIGRAPH on the abdomen with a designated belt about 3 hours before bedtime, and acts as usual until bedtime (but removes the ACTIGRAPH during bathing). The ACTIGRAPH will be worn during bedtime, removed upon waking the next day, and kept at the subject's home during the day. The belt should be the one designated for the study so that there will be no difference in the wearing condition among the study subjects.

After the ACTIGRAPH is collected by the research support organization, the measurement records will be converted into electronic data and analyzed by the Sleep-Wake Rhythm Analysis Laboratory.

10.1.6.3. Salivary melatonin concentration

Saliva samples will be collected using the following saliva collection device on the day before the start of the study, the middle day of prior use (Day 7), the end day of prior use (Day 14), the middle day of switching use (Day 28), and the end day of switching use (Day 35). Samples will then be transported to a laboratory where the melatonin concentration in saliva will be investigated using the following test instruments.

Saliva testing and collection instruments:

Salimetrix, Inc.

Melatonin test kit: SALIMETRICS ASSAY

Saliva collection straws: Saliva Collection Aid

Saliva storage container: Cryovial, 2ml, SalivaBio

Freezer box: 2" Premium Cryostorage Box

Specimen collection and shipping:

(1) The research subject should collect about 0.5 ml of saliva in a container 3 hours before bedtime, 2 hours before bedtime, 1 hour before bedtime, and just before bedtime. The collected specimens should be stored in a freezer at the research subject's home until shipping.

(2) The collected saliva should be packaged in a frozen state and transported to the specimen measurement laboratory via a carrier. Temporary storage will be conducted at a designated storage location as necessary.

(3) Saliva samples are batch-measured at the laboratory.

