Based on these findings, we believe that the disruption of children's circadian rhythms due to exposure to blue light at night from the use of smartphones and tablets may cause children to shift their lives to a nighttime pattern, preventing them from getting proper sleep, and contribute to the risk of developing mental and physical disorders in children, which have been on the increase in recent years. In this study, melatonin concentration, which is directly involved in circadian rhythm,7) will be used as an indicator of the effect on circadian rhythm, and a sham-controlled comparative study will be conducted to examine whether the use of glasses that block blue light increases melatonin concentration before and after bedtime and has a positive effect on sleep and diurnal rhythm. As a secondary evaluation, sleep and wake time will be measured with an actigraph, and sleep-related quality of life will be quantified through a questionnaire for study subjects to evaluate the effects of blue light cutoff on sleep quality, diurnal rhythm, daytime concentration, and mood.

If the effects of blue light on children's circadian rhythm and sleep quality are clarified through this study, it is expected to help in the treatment of mental and physical disorders and disorders, including ADHD, in children, which have been increasing in recent years.

6. objective

To examine whether wearing blue light-cut glasses before and after bedtime increases melatonin levels in school children who are habitually exposed to blue light before bedtime, and whether this has a positive effect on their sleep and diurnal rhythm.

7. study design

Prospective, randomized, sham-controlled, single-blind, crossover, exploratory study

8. study subjects and target number of subjects

School children with a habit of exposure to blue light before bedtime, 40 cases

9. study period

Research period: From the date of approval by the Ethical Review Committee to September 2022

Period of case enrollment: Ethics Review Committee approval date - June 2022

10. research methods

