10.1.6. Survey Methods and Items

The study will be conducted in the home of the research subjects under the supervision of their custodians. Among the potential research subjects who have applied to the recruiting company, the study will be conducted on those research subjects who have given written explanation of the study to the potential research subjects, obtained written consent and assent, and meet the eligibility criteria.

During the study, the study subjects will be instructed to lead a normal life, but to disable the blue light cut mode (night mode, night mode, etc.) on the LED display electronic terminal in consideration of its impact on the study results.

The first wearing of the test spectacles will be on the 1st day and will be completed on the 14th day. The first day of wearing the test spectacles shall be Day 1 and shall be completed on Day 14, and the switching of the spectacles shall be started on Day 22 and completed on Day 35. The first day of the test (Day 1 and Day 22) should be a Friday. In addition, an optional short wearing practice session may be conducted on the day prior to Day 1.

From Day 1 to Day 14 of the prior wearing period, the blue light cut glasses prior wearing group will wear blue light cut glasses and the Siamese glasses prior wearing group will wear Siamese glasses for approximately 3 hours before bedtime every day (14 days of wearing period). Days 15 to 21 will be a non-wearing period for each group, during which the subjects will wear their regular eyeglasses. From Day 22 to Day 35 of the switching period, the subjects in the blue light-cut glasses-first group will wear Siamese glasses, and those in the Siamese glasses-first group will wear blue light-cut glasses for approximately 3 hours before bedtime every day (for 14 days). The test spectacles will be made with the same power as the spectacles that each subject wears in his/her daily life.

During the period of wearing the test spectacles, changes in sleep-wake rhythm will be recorded using an actigraph, and saliva samples will be collected by the research subjects themselves on the day before the start of wearing the spectacles, on the 7th, 14th, 28th and 35th days after the start of wearing, and questionnaires will be administered on the 8th, 15th, 29th and 36th days after the end of wearing the spectacles.

A sleep diary will be filled out daily during the period from Day 1 to Day 36.

10.1.6.1. background information on study subjects

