The time of sleeping and waking, time of use of devices emitting blue light, status of blue light cut mode setting (including protective film status), etc. shall be recorded.

10.2. test equipment

The following products shall be used as the test spectacles. For both blue light cut spectacles and Siamese spectacles, the power of vision correction shall be equivalent to that of the spectacles regularly used by the research subjects in their daily lives.

(1) Eyeglass frames (for both blue light cut glasses and Siamese eyeglasses)

KUF-20S-113~120 Slim Airframe-Kids Basic made by JINS

(2) Eyeglass lenses

［Blue light cut glasses]

JINS SCREEN lens HEAVY made by JINS (blue light cut rate 40%@EN standard)

［Siamese eyeglasses]

Standard clear lenses manufactured by JINS

11. selection of study subjects

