12.2. Secondary endpoints

Assessment of circadian rhythm

2. evaluation of sleepiness, mood, and motivation (modified version of the NRS scale for sleep)

3. evaluation of sleep quality and quantity (Children's Sleep Questionnaire for Elementary School Children/Chronotype Assessment)

Other exploratory evaluation of effects on sleep, etc. 13.

Safety evaluation

This study will not use test instruments for the purpose of treatment, etc., but will ask research subjects to submit saliva for salivary melatonin testing. In addition, medical treatment based on the results of the questionnaire and medical treatment such as ophthalmoscopy during the preparation of the test apparatus will not be performed. In addition, the study will not assess adverse events, as the tests and questionnaires are not invasive to the research subjects, although they may be restrained. An inquiry desk will be set up for emergency inquiries from research subjects and for health-related consultations.

Statistics

14.1. primary endpoint

In the main analysis, time trends of salivary melatonin concentration (4 time points at 0, 1, 2, and 3 hours, starting 3 hours before sleep onset) were tested by repeated two-way ANOVA for Siamese eyeglass wear and blue light cut eyeglass wear (eyeglass type), and the results showed that salivary melatonin concentration was significantly higher for eyeglass type, time trend and interaction ( 14.2. Secondary Assessment Items

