14.2. Secondary endpoints

(1) Evaluation of circadian rhythm

For the effects of wearing Siam glasses and blue light cut glasses on sleep and diurnal rhythm, objective sleep indices will be analyzed by automatic analysis of actigraph data, followed by visual correction under blind conditions as necessary. Sleep parameters such as time to fall asleep, time to wake up, total time to fall asleep, total sleep time, latency to fall asleep, mid-awake, and sleep efficiency are averaged from Monday to Thursday of each week and compared.

(2) Evaluation of sleepiness, mood, motivation, sleep quality and quantity

For subjective evaluation using a questionnaire, the total scores for I excessive daytime sleepiness, II daytime behavior, III morning symptoms, IV insomnia/rhythm, V holiday sleep rhythm, and VI chronotype were calculated for each week, and the data for each week for the Siam glasses wearer and blue light cut glasses wearer were compared. Statistical analysis was conducted to determine whether there was a significant change in the data with and without blue light cutoff glasses when wearing Siamese glasses or blue light cutoff glasses.

For the NRS, statistical analysis will be conducted to see if there is a significant change in each item for each week when wearing Siamese eyeglasses and when wearing blue light cut eyeglasses, using the corresponding t-tests.

Through these statistical analyses, we will examine whether wearing blue light-cut glasses before bedtime reduces exposure to blue light from smartphones and other devices, prevents the suppression of melatonin release before and after bedtime, and consequently improves sleep quality and prevents delays in the diurnal rhythm.

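### Saliva samples are timed from an undefined bedtime that the glasses may shift, so clock time and melatonin level can be confounded in the primary comparison

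*Protocol*

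**What the plan says.** Section 10.1.6.3 has the child collect saliva at "3 hours before bedtime, 2 hours before bedtime, 1 hour before bedtime, and just before bedtime", on the evening before the start and on Days 7, 14, 28 and 35. It gives no clock times and does not define bedtime.

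Section 14.1 analyses melatonin by a repeated two-way ANOVA of lens type and time, with the time axis given as "4 time points at 0, 1, 2, and 3 hours, starting 3 hours before sleep onset".

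Bedtime is not held fixed: under section 10.1.6, "the study subjects will be instructed to lead a normal life".

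The protocol also expects timing to respond to the lens. The background section says melatonin "will be used as an indicator of the effect on circadian rhythm". Section 14.2 will examine whether wearing the glasses "consequently improves sleep quality and prevents delays in the diurnal rhythm". It lists "Sleep parameters such as time to fall asleep, time to wake up, total time to fall asleep" among the actigraph outcomes.

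**The concern.** Melatonin is expected to rise through the evening, so a measured value depends on when the sample is taken as well as on the lens. If sampling is counted back from a bedtime that the lens can move, the sampling clock moves with the treatment. The two lenses are then compared at different clock times, and the primary contrast mixes three things: a change in level, a change in melatonin phase and a change in bedtime.

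The crossover does not remove this, because a bedtime shift caused by the lens travels with the lens. Having all sampling evenings on the same weekday balances ordinary weekday variation but not a treatment effect on bedtime.

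The two anchors are also different events. Sleep onset follows bedtime by the sleep latency, which section 14.2 analyses as an outcome, and it is not known when the samples are taken.

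**Working it through.** The protocol gives no figure to reproduce: it states no melatonin level, slope, variance or expected effect. The check is therefore of logic, with illustrative numbers.

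**Weekdays.** Days 1 and 22 are Fridays (section 10.1.6). The evening before Day 1 and Days 7, 14, 28 and 35 are therefore all Thursdays.

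**Bedtime moves, melatonin phase does not.** Assume melatonin rises r-fold per hour, with r = 1.3 to 2 (not in the documents). A sample taken d minutes earlier is multiplied by r^(−d/60).

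| r per hour | d = 15 min | d = 30 min |
|---|---|---|
| 1.3 | 0.937 (−6%) | 0.877 (−12%) |
| 1.5 | 0.904 (−10%) | 0.816 (−18%) |
| 2 | 0.841 (−16%) | 0.707 (−29%) |

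**Phase and bedtime move in different combinations.** Assume C(t) = 20/(1 + exp(−(t − m)/s)) pg/mL, with midpoint m = 21:00, s = 0.6 h and sham bedtime 22:00 (none of these from the documents). Under sham, the samples at 19:00, 20:00, 21:00 and 22:00 are 0.69, 3.18, 10.00 and 16.82. Their sum is 30.69 and their mean 7.67. Change in the four-sample mean with samples anchored to actual bedtime:

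- Phase and bedtime both 0.5 h earlier: 0.00. Both t and m fall by the same amount, so t − m is unchanged. This holds for any curve that shifts without changing shape.
- Phase 0.5 h earlier, bedtime 0.25 h earlier: +1.16 (+15%), half the shift removed.
- Phase 0.5 h earlier, bedtime unchanged: +2.33 (+30%), fully seen.
- Bedtime 0.5 h earlier, phase unchanged: −2.22 (−29%), a spurious fall under the blue-cut lens.
- True 10% rise in level, phase and bedtime moving together: 0.10 × 7.67 = +0.77, fully kept.
- True 10% rise in level, bedtime alone 0.25 h earlier: the unadjusted mean falls by 1.13 to 6.54, and 1.1 × 6.54 − 7.67 = −0.48, so the sign reverses.

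**Same clock times under both lenses.** If all four samples are taken as set, the 0.5 h phase advance gives +2.33 in this case. It gives +1.8 to +2.5 pg/mL (+19% to +47%) over m = 20:30 to 21:30 and s = 0.4 to 1.0 h. If bedtime also moves to 21:30 and the last sample is taken then, the four values are 1.52, 6.06, 13.94 and 16.82, with sum 38.34. The change is (38.34 − 30.69)/4 = +1.91 (+25%), so most of the effect is still seen.

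**The case against.** The strongest reply is that the protocol never says sampling follows each evening's actual bedtime. A sample due three hours ahead must be timed from an expected bedtime. Irregular sleepers are excluded, guardians supervise at home, and all sampling evenings are Thursdays. If families use one habitual bedtime throughout, the problem largely disappears. This stands as a limit on the concern, but the text does not fix that reading.

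Second, the stated melatonin hypothesis is about level: that blocking blue light "increases melatonin concentration before and after bedtime". Sampling relative to bedtime suits that question, and sleep timing is assessed separately by actigraphy. This also stands in part. The level effect remains measurable, though biased if bedtime shifts alone, and the protocol also makes melatonin its circadian indicator.

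Third, the lenses are worn for about the last three hours before bed, so bedtime-anchored samples line up with roughly 0, 1, 2 and 3 hours of wear. Fixed clock times give up that alignment if bedtime moves. This is a real cost of the change.

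Fourth, the diary records "The time of sleeping and waking, time of use of devices emitting blue light", so approximate sample times on Days 7, 14, 28 and 35 could be rebuilt, and adjustment is ordinary SAP content. But the protocol does not say that the clock time of each sample is recorded. No analysis plan can recover exact times that were not collected.

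Finally, sleep onset in section 14.1 may be only a translation variant of bedtime, since the four points match one to one. The main argument does not depend on this wording.

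**Conclusion.** The concern holds in a conditional form. The primary endpoint's time axis hangs on an undefined bedtime that the protocol's own hypothesis allows the lens to move. If the anchor is actual bedtime and it differs by lens, a phase advance that bedtime follows equally is lost, and an earlier bedtime alone biases the comparison against the blue-cut lens.

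A reader might infer that any earlier bedtime or phase advance is cancelled out of the primary endpoint. The documents do not support that. Complete cancellation needs phase and bedtime to move by the same amount. A phase advance with unchanged bedtime is fully seen, an earlier bedtime alone produces bias rather than cancellation, and a pure level effect survives when relative timing is unchanged.

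The size is unknown. The 6% to 16% for a 15-minute shift rests on an assumed 1.3 to 2-fold hourly rise, an assumed shift and an unchanged phase. Nothing in the protocol indicates how far bedtime would move. The change should be made before sampling starts, because it governs what is collected.

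**What to change.** - In section 10.1.6.3, define the anchor once per child as the habitual school-night bedtime at enrolment. Use the resulting four clock times on all five Thursday evenings, in both periods.
- Record the actual clock time of every sample, for example on the tube.
- In section 14.1, replace sleep onset with the same anchor as section 10.1.6.3, and use the recorded sample time in the analysis, at least as a sensitivity analysis.

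The cost is a short addition to the saliva instructions, a line in section 14.1 and one more item for families to write down.

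There are two downsides to state. If a child goes to bed early, the last sample is taken before its set time and must be analysed at its recorded time. If actual bedtime moves, lens-wear duration at each sample may differ between periods; the diary's wear times and the recorded sample times allow this to be checked. At fixed clock times a higher value may also reflect level, phase or both, and the contrast alone does not separate them.

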10.1.6.4 Research subject questionnaire

The following research subject questionnaires will be administered on the day following the middle day of prior use (Day 8), the day following the end of prior use (Day 15), the day following the middle day of switching use (Day 29), and the day following the end of switching use (Day 36).

Questionnaire items:

(1) Elementary school version of the Children's Sleep Questionnaire (excerpts)/Chronotype Assessment (Appendix C)

A total of 23 questions (6 choices), including 4 questions on I excessive daytime sleepiness, II daytime behavior, III morning symptoms, IV insomnia/rhythm, V holiday sleep rhythm, and VI chronotype in the days preceding the questionnaire response.

(2) Modified NRS Scale for Sleep (Appendix D)

The NRS will be used to evaluate the state of sleep at the time of answering the questionnaire on an 11-point scale, with 5 items: "awake, not sleepy, feeling good, motivated, and having a good appetite".

Study subjects will complete a paper questionnaire after waking up, and each will be sent by mail to the research office support organization.

The collected questionnaires will be converted into electronic data at the research secretariat support organization, and analyzed at the Sleep/Wake Rhythm Analysis Organization.

10.1.6.5. Sleep diary (information on test equipment use, sleep duration and electronic terminal use)

The following information on the use of the test equipment and other devices shall be recorded in the sleep diary (Appendix E) during the preceding and switching periods. In addition, sleep time and electronic device use time information shall be recorded in the sleep diary during the prior use, non-use, and switchover periods.

(1) Information on wearing of test equipment, etc.

The wearing time of the test spectacles will be recorded. The recorded sleep diaries and subject questionnaires will be collected on days 15 and 36, and mailed to the research secretariat support organization, respectively. The collected questionnaires will be converted into electronic data at the research secretariat support organization, and analyzed by the Sleep-Wake Rhythm Analysis Laboratory. In addition, the data from the sleep diary collected on the 15th day will be used to confirm compliance with wearing the study glasses.

(2) Sleep time and electronic device use time information

The time of sleeping and waking, time of use of devices emitting blue light, status of blue light cut mode setting (including protective film status), etc. shall be recorded.

10.2. test equipment

The following products shall be used as the test spectacles. For both blue light cut spectacles and Siamese spectacles, the power of vision correction shall be equivalent to that of the spectacles regularly used by the research subjects in their daily lives.

(1) Eyeglass frames (for both blue light cut glasses and Siamese eyeglasses)

KUF-20S-113~120 Slim Airframe-Kids Basic made by JINS

(2) Eyeglass lenses

［Blue light cut glasses]

JINS SCREEN lens HEAVY made by JINS (blue light cut rate 40%@EN standard)

［Siamese eyeglasses]

Standard clear lenses manufactured by JINS

11. selection of study subjects

11.1 Selection and Exclusion Criteria

Among school children who have a habit of being exposed to blue light before bedtime, those who meet the following selection criteria and do not violate the exclusion criteria will be included in the study.

(1) Selection criteria

(1) Healthy elementary school boys aged 9-12 years at the time of obtaining consent

(ii) Those who regularly use glasses with vision correction in daily life

(iii) Those who are habitually exposed to blue light from LED displays, etc. for an average of one hour or more per day before bedtime.

(iv) Those who have obtained written consent for participation in this study from themselves and their parent or guardian.

(2) Exclusion criteria

(1) Those who use the following lenses, which cannot be made according to the specifications of the lenses used in this study, in their regular eyeglasses in daily life.

Lenses with power that falls outside the following ranges (myopia: SPH: -8.00 to 0D, CYL: -4.00 to 0D, hyperopia: SPH: 0 to +4.00D, CYL: 0 to +4.00D) or lenses other than single vision lenses such as progressive or prismatic lenses

(ii) Those who are aware that the power of the spectacles they regularly use in their daily lives is not appropriate and need to have their power re-measured at a hospital or ophthalmologist's office, etc.

(iii) Those whose eyeglass lenses used regularly in daily life cannot be checked by eyeglass stores.

(iv) Those who are taking drugs or supplements that affect sleep, autonomic nerves, or central nervous system.

(v) Those who have a history of or are suffering from sleep disorder, mental disorder, immune/allergic disease, metabolic disorder, corneal disorder, retinal disorder, dry eye, eye strain, etc. (vi) Those who are taking medication for hay fever, etc.

(vi) Those who need drug treatment for hay fever, etc.

(vii) Persons with infectious diseases stipulated in the Infectious Diseases Control Law and blood-borne diseases (HBV, HCV, HIV, syphilis) (including persons in close contact)

(viii) Persons who cannot properly wear the examination equipment under the supervision of a person with parental authority before going to bed.

(ix) Persons with irregular sleeping habits

(x) Persons who plan to change their living environment during participation in the research.

(xi) Other subjects who are deemed inappropriate as research subjects by the physician.

